# Shared decision making in type 2 diabetes with a support decision tool that takes into account clinical factors, the intensity of treatment and patient preferences: design of a cluster randomised (OPTIMAL) trial

**DOI:** 10.1186/s12875-015-0230-0

**Published:** 2015-02-27

**Keywords:** Decision support tool, Personalised diabetes treatment, Shared decision making, Goal setting

## Abstract

**Background:**

No more than 10-15% of type 2 diabetes mellitus (T2DM) patients achieve all treatment goals regarding glycaemic control, lipids and blood pressure. Shared decision making (SDM) should increase that percentage; however, not all support decision tools are appropriate. Because the ADDITION-Europe study demonstrated two (almost) equally effective treatments but with slightly different intensities, it may be a good starting point to discuss with the patients their diabetes treatment, taking into account both the intensity of treatment, clinical factors and patients’ preferences. We aim to evaluate whether such an approach increases the proportion of patients that achieve all three treatment goals.

**Methods:**

In a cluster-randomised trial including 40 general practices, that participated until 2009 in the ADDITION Study, 150 T2DM patients 60–80 years, known with T2DM for 8-15 years, will be included. Practices are randomised a second time, i.e. intervention practices in the ADDITION study could be control practices in the current study and vice versa. For the GPs from the intervention group a 2-hour training in SDM was developed as well as a decision support tool to be used during the consultation. GPs plan the first visit with the patients to decide on the intensity of the treatment, personalised targets and the priorities of treatment. The control group will continue with the treatment they were allocated to in the ADDITION study. Follow-up: 24 months. The primary outcome is the proportion of patients who achieve all three treatment goals. Secondary outcomes are the proportion of patients who achieve five treatment goals (HbA1c, blood pressure, total cholesterol, body weight, not smoking), evaluation of the SDM process (SDM-Q9 and CPS), satisfaction with the treatment (DTSQ), wellbeing and quality of life (W-BQ12, ADD QoL-19), health status (SF-36, EQ-5D) and coping (DCMQ). The proportions of achieved treatment goals will be compared between both groups. For the secondary outcomes mixed models will be used. The Medical Research Ethics Committee of the University Medical Centre Utrecht has approved the study protocol (Protocol number: 11-153).

**Discussion:**

This trial will provide evidence whether an intervention with a multi-faceted decision support tool increases the proportion of achieved personalised goals in type 2 diabetes patients.

**Trial registration:**

NCT02285881, November 4, 2014

## Background

Successful prevention of complications in the increasing number of patients with type 2 diabetes (T2DM) appears to be difficult. In primary care no more than 10-15% of the patients with T2DM achieve all three treatment targets (glycaemic control, lipids, blood pressure) [1-6]. For separate targets much higher percentages of about 30-70% are reported [2-6]. Therefore, it has been suggested that a more personalised and patient centred approach might increase the proportion of patients who successfully reach all their treatment targets [7,8]. To personalise treatment targets for HbA1c, lipids, blood pressure, weight loss and smoking cessation, several factors have to be considered in order to encourage active participation of patients in evidence based clinical decision making.

Physicians are advised to consider the patients’ age, motivation, risk of hypoglycaemia, diabetes duration, comorbidity and established vascular complications in setting the glucose control target [8,9]. For statin therapy, physicians should consider the patient’s individual cholesterol level, his/her risk for cardiovascular mortality, age and T2DM duration [10]. The blood pressure target for patients with T2DM is below 140/80 [11,12], but for older patients a less strict treatment target may result in a higher survival rate [13]. With regard to weight control, physicians have to consider the side effects of weight gain of medication. Intensive lifestyle modification remains an elusive gold standard for weight reduction [14] Although smoking cessation has been associated with weight gain, it is recommended as a routine component of the treatment of diabetes; however, evidence to guide best practice is limited [15].

To achieve and maintain treatment targets, not only individual clinical characteristics should be considered, but also patients’ preferences for treatment intensity. Generally speaking, the doctor is the expert on medicine, while the patient is the expert on his or her priorities [16]. Shared decision making (SDM) is an approach that takes into account both the clinical evidence for treatment goals as well as the patient’s preferences. SDM is defined as ‘an approach where clinicians and patients make decisions together, using the best available evidence’ [17]. It promotes patient autonomy and patient engagement in the treatment decision making by giving the patient an active role in weighting the benefits and harms of more than one evidence based treatment option [17]. Although SDM is promising for patients with chronic diseases by setting realistic treatment targets, such an extensive approach had not been broadly studied in T2DM patients before 2008 [18]. Recently the effects a patient oriented decision aid for SDM and goal setting in T2DM patients on patient empowerment and treatment decisions have been published [19]. No effect was found on empowerment, the decision aid was not used to measure the effect on clinical outcomes and achievement of goals.

Because SDM is especially useful when there are two or more equally beneficial treatment options, the results of the ADDITION-Europe study, in which the Netherlands participated, could be used in a SDM approach in patients with T2DM. The ADDITION study included screen detected T2DM patients and compared an intensive multifactorial treatment of HbA1c, cholesterol, blood pressure and body weight with less intensive usual care according to national guidelines. The intensive treatment was associated with a significant increase in prescribed medications and a non-significant 17% reduction of cardiovascular events and death after 5 years. However, the rate of cardiovascular events seemed to diverge after 4 years of follow-up. It was concluded that intensified treatment and treatment according to national guidelines can theoretically be equally effective [1]. Based on the results of the ADDITION study, it is questionable which evidence based treatment advice the diabetes care provider should give to the T2DM patient. There is no decisive evidence for either option. This situation is very appropriate for treatment decisions that incorporate the patient’s preferences.

In a recent statement of both the American Diabetes Association (ADA) and the European Association for the Study of Diabetes (EASD) personalised and patient-centred care is mentioned as the cornerstone of the treatment of patients with T2DM. The use of a decision support tool is strongly advocated [8]. A decision support tool can encourage active patient participation in many evidence-based healthcare decisions [20-22]. In the last decade decision support tools have been developed to support the achievement of cardiometabolic goals and to select patient-centred treatment options for lifestyle modifications or medication use [8,23-28]. However, most of them focus on a single risk factor [25], on only the patients’ preferences [26,27] or on some individual clinical characteristics [28]. We hypothesise that a decision support tool that takes into account both treatment intensity, patient’s clinical characteristics and patient’s preferences can facilitate a SDM process and will be effective in achieving treatment targets. We aim to evaluate whether such an approach increases the proportion of treatment targets that T2DM patients achieve.

The following research questions are addressed:What is the effect of shared decision making with a multi-faceted decision support tool on the percentage of patients with T2DM that achieve all individualised treatment targets for HbA1c, blood pressure and LDL-cholesterol; and to identify determinants for achieving all individualised treatment targets.What is the effect of shared decision making with a multi-faceted decision support tool on treatment satisfaction, quality of life, health status, well-being and on coping styles?What is the level of SDM-knowledge/attitude of the GPs from both treatment groups after 24 months?

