**Figure 2 Fig2:**
[figure not shown]
**Decision support tool.**Visits during the OPTIMAL study.During the first visit, and guided by the decision tool, the GP and the patient discuss the two evidence based T2DM treatments. The GP will explain the pros and cons of each option, and the treatment targets that should be achieved, depending on the option that is chosen. The GP should explain that both treatments are equally suitable for treating T2DM. Next, the patient’s preferences and lifestyle habits are discussed against the background of the patient’s most recent values of HbA1c, lipids, blood pressure, body weight and smoking habits. Then the GP and the patient will together decide on the preferred treatment option and the accompanying treatment targets. For a patient who underwent the intensified treatment in the ADDITION study and did not change it after the end of ADDITION, this visit provides him/her the opportunity to choose a less intensive treatment. Also the other way around is possible. The patient will prioritise the five treatment targets (HbA1c, cholesterol, blood pressure, body weight, smoking habits) for the first 12 months. The target with the highest priority will get the most attention and require the most effort of both the patient and GP. There will be no pre-defined way in how the patients should reach their targets; the patient and the GP need to determine this way together in a final step in the decision process. The patient and GP decide whether medication changes and/or lifestyle changes should be made in order to reach the prioritised targets. During the second and third OPTIMAL visit (12 and 24 months later) the patient and GP evaluate the decisions they made during the first visit using the decision support tool. The priority of the treatment targets can be changed during these visits, but not the choice between the two treatment options (ADDITION protocol or the less intensive protocol). During the third and final visit the patient and the GP will decide whether or not to keep to the chosen treatment option. Between the first and third visit, three monthly T2DM visits will take place either with the GP or the practice nurse.

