### Control group

Patients in the control practices will receive treatment-as-before. Also, the GPs will not be asked to engage in a SDM process, nor be trained to do this and they will not be offered the decision support tool. The GP will treat the patients as they were used to since the ending of the ADDITION study (2009), either following the national guidelines or the ADDITION intensive treatment algorithm, each with their respective targets [1].

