### Outcome measures

Primary outcome will be the proportion of patients that achieve all the three treatment goals for HbA1c, blood pressure, and total cholesterol .In addition to identify determinants of better performing patients for the primary outcome will be performed taken into account the interaction of SDM with age, gender, education level, duration of diabetes and comorbidities.

Secondary outcomes:The proportion of patients that achieve the all five treatment goals for HbA1c, blood pressure, total and LDL- cholesterol, body weight, and smoking.The following patient reported outcomes: diabetes treatment satisfaction, perceived quality of life, health status, well-being, and coping style.A process evaluation of the shared decision making ability of the general practitioners during the complete study. Outcome on GP level: the level of SDM-knowledge/attitude.

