## Discussion

The treatment of T2DM is mostly target driven. However, only a low percentage of all patients with T2DM achieve all goals. SDM and goal setting can be useful to increase the percentage of patients that achieve all targets. However, the decision support tool to be used in SDM should likely not only focus on the clinical factors of the patients but also on the patient’s preferences, because each of these variables may affect the optimal treatment targets. Besides, the decision support tool should be used in a SDM process during more than one consultation [8]. The results of the ADDITION trial, in which half of the participants of the current study also participated, offers a unique opportunity to discuss with the patient two almost equally effective treatment strategies.

In the current cluster-randomised controlled trial we will evaluate the effectiveness of such a repeated use of a decision support tool, taking into account both the intensity of treatment, individual clinical factors and the patients’ experiences and preferences. We hypothesise that the SDM process with such a well-balanced decision support tool will improve the percentage of patients that achieve all three individual goals compared to the control group, making SDM really beneficial.

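### The stated question scores success on individualised targets, which only the intervention arm sets after randomisation, and the outcome definition names no yardstick common to both arms

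*Protocol article*

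**What the plan says.** Three places in the protocol article define success by personal targets.

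- Background, first research question: the percentage that "achieve all individualised treatment targets for HbA1c, blood pressure and LDL-cholesterol".
- Abstract, Discussion: the trial is to show whether the intervention "increases the proportion of achieved personalised goals in type 2 diabetes patients".
- Discussion: the hypothesis is that SDM will "improve the percentage of patients that achieve all three individual goals compared to the control group".

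The Outcome measures section is worded differently: "Primary outcome will be the proportion of patients that achieve all the three treatment goals for HbA1c, blood pressure, and total cholesterol". It names neither individual targets nor a common target set, and the Statistical analyses section adds none.

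The target sets arise differently in the two arms. Under Intervention (visits during the study), the GP explains the two protocols and "the treatment targets that should be achieved, depending on the option that is chosen". The patient's latest values are discussed, and patient and GP then decide together on the option and its targets. A patient on intensified treatment may move to the less intensive option, or the reverse. The option stays fixed until the final visit. Under Control group, GPs continue as they have done since 2009, "either following the national guidelines or the ADDITION intensive treatment algorithm, each with their respective targets".

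**The concern.** If each patient is scored on his or her own targets, the yardstick is part of what the intervention changes. Randomising practices makes the arms comparable in their risk factors on average. It cannot do the same for a threshold that is selected after randomisation, in one arm only, with current values in view. Intention-to-treat analysis and adjustment for clustering leave this untouched.

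A difference in the primary endpoint could then reflect better risk-factor control, a different mix of thresholds, or both. A move towards the looser set would flatter the intervention, and a move towards the stricter set would penalise it. If the outcome section instead intends one common set, it does not match the research question and the hypothesis. The text needs a change on either reading.

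**Working it through.** **The plan's own figure.** Sample size section: 10% vs 30%, two-sided 5%, 80% power, 10% drop-out, 65 per group; design effect 1.125, then 73.

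- Unpooled normal formula: (1.960 + 0.842)² × (0.10×0.90 + 0.30×0.70) / 0.20² = 58.9, rounded up to 59. With drop-out, 58.9/0.9 = 65.4, or 59 × 1.1 = 65.
- Design effect: 1 + (6 − 1) × 0.025 = 1.125, and 65 × 1.125 = 73.1.

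The figures reproduce and are not in dispute. The effective size per arm, after drop-out and clustering, is 73 × 0.9 / 1.125 = 58.4.

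**The artefact.** Suppose the risk factors are distributed identically in both arms. Let pS and pL be the pass rates on the stricter and looser sets, and c and q the shares of control and intervention patients scored on the stricter set.

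- Control rate: c·pS + (1 − c)·pL
- Intervention rate: q·pS + (1 − q)·pL
- Difference (intervention minus control): (c − q)(pL − pS)

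This is zero only if the two arms have the same mix of sets or the sets are equally hard to meet. If every patient is scored on one set, it is exactly zero.

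**Illustration.** The article gives no pass rate per set and no expected uptake of either option, and the target values are in a figure not available here. All of the following are therefore assumptions: pS = 10%, pL = 20% or 30%, c = 50%, and 75% or 100% of intervention patients on the looser set (q = 25% or 0). The last column is the chance of p<0.05 in favour of the intervention, from a pooled two-proportion z-test with 58.4 per arm; the nominal value in that direction is 2.5%.

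| pL | On looser set (intervention) | Control | Intervention | Difference | Favourable p<0.05 |
|---|---|---|---|---|---|
| 20% | 75% | 15% | 17.5% | 2.5 points | 5.5% |
| 20% | 100% | 15% | 20% | 5 points | 10.5% |
| 30% | 75% | 20% | 25% | 5 points | 9.4% |
| 30% | 100% | 20% | 30% | 10 points | 23.7% |

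The two largest probabilities need every intervention patient to be on the looser set.

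**Reverse direction.** If every intervention patient were on the stricter set (q = 1), the differences would be (0.5 − 1) × 10 = −5 points and (0.5 − 1) × 20 = −10 points.

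**Controls held at the planned 10%.** The rates above put controls at 15–20%, above the plan's 10%. Fixing controls at 10% with c = 50%, pS/pL between 0.25 and 0.5 and q between 0 and 25%, the difference is about +2 to +6 points. The two-sided rejection probability is then about 6% to 16% against a nominal 5%. For example, pS = 4%, pL = 16% and q = 0 give 16% vs 10%, a relative risk of 1.6.

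**The case against.** The strongest reply is that own-target scoring is inferred. No sentence says that controls are scored on the targets of their regimen; the Control group section describes treatment. The outcome section does not use the word individualised. The Sample size section expects about 10% to have reached three targets at the start, before any option is chosen, which fits a common yardstick. This stands as a limit on the claim: the article does not settle the rule. It does not clear the plan, because the research question, the abstract's conclusion and the hypothesis all point to personal targets.

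Several stronger readings are tempting, and the article does not support them.

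- *Patients set their own goals freely.* They choose jointly with the GP between two fixed protocols, and the option is locked until the final visit.
- *Controls who were never in the earlier trial have no targets.* The abstract says "The control group will continue with the treatment they were allocated to in the ADDITION study", while the Discussion describes the earlier trial as one "in which half of the participants of the current study also participated". Yet the Control group section refers to what the GP was used to doing, which largely supplies a practice-level set. The abstract is loose shorthand.
- *The 10% planning rate is a usual-care figure.* The article describes it as a primary-care figure and an estimate, and does not tie it to usual-care targets.
- *The trial cannot answer its question.* Reaching agreed goals is the stated aim and a legitimate one. What cannot be separated is a change of goals from a change in risk factors.
- *Nothing could reveal a clinical effect.* HbA1c, blood pressure and cholesterol are recorded yearly in both arms, and a supportive comparison may sit in a fuller document.

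Making a common set primary is also not neutral: it narrows the question, and a strict common set would count as failures some patients who met the looser targets they had agreed.

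**Conclusion.** The point holds in conditional form. The article gives two incompatible accounts of the primary yardstick. Under the one that its question and hypothesis state, the outcome definition differs by arm and is affected by the intervention. A between-arm difference of (c − q)(pL − pS) can then arise with no clinical change, in either direction.

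The structure of this bias follows from the text; its size does not. The range of 2.5 to 10 points, up to half of the planned 20-point effect, rests wholly on the assumed pass rates, the even split of controls and the 75–100% uptake. So does the 5.5% to 24% chance of a favourable result. With controls at 10% and moderate inputs, the difference is about 2 to 6 points. None of these is a prediction for this trial. The matter should be settled before analysis, because the meaning of the primary result depends on it.

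**What to change.** 1. Reconcile the Outcome measures section with the research question and the hypothesis, and state one scoring rule for both arms. Name the lipid component too: the research question has LDL-cholesterol and the outcome section total cholesterol, and no set can be scored until this is fixed.
2. Pre-specify an analysis that scores every patient in both arms at 24 months against one named target set already in the decision tool, preferably as the primary between-arm test. Repeat it with the other set. The trial team should name the set in advance.
3. Report attainment of own targets alongside it, with the option chosen in the intervention arm and the regimen followed in the control arm.
4. Add baseline-adjusted between-arm differences in HbA1c, blood pressure and cholesterol.
5. If own-target attainment stays primary, limit its conclusion to reaching agreed goals, and claim better risk-factor control only if the common-target analysis agrees.

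The cost is protocol and analysis-plan wording and a re-scoring of values already on the yearly case report form; no new patients or measurements are needed. The downside is that the personalised result may become supportive, and the 10% vs 30% planning rates must be re-justified for the named set.

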## Methods

### Study design and setting

The OPTIMAL study is a cluster-randomised trial with randomisation at practice-level and two years follow-up. We developed an intervention to promote SDM with a decision support tool based on the results of the above mentioned ADDITION-Europe study. Since for an optimal SDM approach physicians should have some experience with all treatment options, patients are recruited from the 79 general practices that participated in the ADDITION study [29]. For the OPTIMAL study practices are randomised again (Figure 1). GPs in the intervention group were trained in SDM (see further).

**Figure 1 Fig1:**
[figure not shown]
**Flow chart.**

### Practices and patients

Eligible GPs are those who included at least included one patient in the ADDITION-study. For the OPTIMAL study each GP should include at least two more or less comparable patients: 1. Former ‘ADDITION’ patients diagnosed with T2DM in 2002-2004 by screening, aged between 50-70 years at that time and having participated in the ADDITION study that ended in 2009; 2. Patients between 60 and 80 years in 2012-2014, known with type 2 diabetes for 8-12 years but not diagnosed in the ADDITION study. Patients will be excluded if they have a history of alcoholism, drug abuse, psychosis, personality disorder or another emotional, psychological or intellectual problem that is likely to invalidate informed consent, or limit the ability of the individual to comply with the protocol requirements. Also, patients with a limited life expectancy will not be approached.

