### Randomisation

Randomisation is executed at the research center at practice-level, without any stratification. It is not possible to blind participants and GPs for the treatment allocation. Practices are randomised a second time, i.e. intervention practices in the ADDITION study could be control practices in the current study and vice versa.

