### Sample size

As stated in the Introduction, only 10-15% of T2DM patients achieve all three treatment targets for both HbA1c, lipids and blood pressure. We estimate the percentage of patients that already has reached three targets at the start of the study will be approximately 10%. We hypothesise that in the OPTIMAL study, after two years of follow-up, the intervention group will show an increase of this percentage until 30% (about 10% increase per year), whereas in the treatment-as-before-group this percentage will stay at 10%. Assuming a two-sided significance level of 5%, with alpha 0.05 and power of 80% and with a drop-out of 10%, 65 patients will be needed in each treatment group (Department of Statistics Sample Size Calculator, University of British Columbia). Because the OPTIMAL study is a cluster randomised study the sample size will require an correction for the cluster effect. The used correction factor is equal to [1 + (m - 1) r], where ‘m’ is the total amount of eligible patient per practice (approximately 6), and ‘r’ the within-cluster correlation coefficient. For ‘r’ we use a within-cluster correlation coefficient of 0.025, based on the cluster correlation found in the ADDITION-Europe study. When taken the cluster effect (1.125) in to account, 73 patients per group are needed.

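### Patients enter through GPs who cannot be blinded, under a loose inclusion rule, and the primary model as described corrects only for clustering, so arm-dependent recruitment would go uncorrected

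*Protocol article*

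**What the plan says.** All references are to the protocol article.

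- **Randomisation:** "Randomisation is executed at the research center at practice-level, without any stratification". The same section adds: "It is not possible to blind participants and GPs for the treatment allocation".
- **Practices and patients:** "each GP should include at least two more or less comparable patients". Two types are named: former participants of the earlier ADDITION trial, and other patients of similar age and diabetes duration. The exclusions include a judgement on whether the patient could comply with the protocol, and a limited life expectancy with no threshold given.
- **Sample size:** the cluster size m in the design effect is described as the "total amount of eligible patient per practice (approximately 6" patients.
- **Abstract, Methods:** "In a cluster-randomised trial including 40 general practices", with a total of "150 T2DM patients".
- **Study design and setting:** the recruitment pool is wider: "patients are recruited from the 79 general practices that participated in the ADDITION study".
- **Statistical analyses:** the between-group comparison is by intention to treat, with generalized linear models that correct for practice-level clustering. Patient characteristics enter the primary outcome only in a repeat analysis that looks for interactions with the intervention. No baseline adjustment of the main comparison is described.
- **Measurements, data collection:** GPs in both groups report HbA1c, blood pressure and cholesterol every year on a case report form.

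**The concern.** Randomising practices balances practices. It balances patients only if the way patients enter does not depend on the arm. Here the person who includes patients cannot be blinded, the rule sets a floor of two and a loose comparability criterion, and two exclusions call for judgement.

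The task also differs by arm. An intervention GP has been trained for, and must hold, a demanding shared-decision visit. A control GP continues treatment as before. An intervention GP could reasonably prefer engaged patients for that visit, and a patient who knows what is on offer could accept or decline for the same reason.

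If that happens, the arms differ at the start in how close patients are to their goals. The intention-to-treat comparison keeps that difference, because it analyses patients as included. A correction for clustering changes the standard error, not the imbalance.

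**Working it through.** **Inputs, all from the article:** 40 practices and 150 patients (Abstract); about 6 eligible per practice, 10% at goal at the start, control staying at 10%, intervention reaching 30%, dropout 10%, within-cluster correlation 0.025 (Sample size).

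**1. The plan's own sample size.** Two proportions, unpooled normal formula, two-sided 5%, power 80%:

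n = (1.960 + 0.842)² × (0.10 × 0.90 + 0.30 × 0.70) / 0.20² = 58.9 per group.

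With dropout: 58.9 / 0.90 = 65.4 (stated: 65). Design effect: 1 + (6 − 1) × 0.025 = 1.125. Then 65 × 1.125 = 73.1 (stated: 73). The figures reproduce, and 2 × 73 = 146 agrees with a target of 150.

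**2. Room between eligible and included.**
- Included per practice: 150 / 40 = 3.75 (146 / 40 = 3.65).
- Eligible in total: 40 × 6 = 240.
- Share included: 150 / 240 = 62.5%.
- If every eligible patient entered, 150 / 6 = 25 practices would be enough, so the planned 40 do not fit all-eligible inclusion at m = 6.
- If all 79 practices of the pool took part: 150 / 79 = 1.9 per practice, still well below 6.

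**3. What arm-dependent inclusion could do to the starting point.** Assume, as the plan does for its patients, that 10% are at goal, and apply this to all eligible patients. Let those at goal be k times as likely to be included as the rest, in one arm only. The proportion at goal among those included is

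p = 0.10k / (0.10k + 0.90).

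| k | Calculation | Proportion at goal at start | Excess over 10% |
|---|---|---|---|
| 1 | 0.100 / 1.000 | 10.0% | 0 points |
| 1.25 | 0.125 / 1.025 | 12.2% | 2.2 points |
| 1.5 | 0.150 / 1.050 | 14.3% | 4.3 points |

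Both values of k are possible with 62.5% included. At k = 1.5 the rest are included at 0.625 / 1.05 = 59.5%, and those at goal at 1.5 × 59.5% = 89.3%.

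**4. Set against the planned effect.** If such an excess carried through to 24 months unchanged, it would be 2.2 / 20 = 11% to 4.3 / 20 = 21% of the planned 20-point difference. The values of k are assumptions; the documents give nothing from which to estimate them.

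**The case against.** The strongest reply is that the article does not describe the order of events. Who lists patients, who invites them, and whether this comes before disclosure are procedures that a full protocol may settle, and the flow chart is not shown. The statement on blinding is the usual one for an open intervention and does not say that GPs knew their arm when patients were identified. The verb tenses do not decide it either: intervention GPs are described as already trained in one section and as being trained in another, while patients are still to be included. This stands. The article does not show that inclusion followed disclosure, and the point does not claim that it did.

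A reader might infer that GPs choose about 4 of 6 patients. The documents do not support that. The 3.75 is a planned total divided by a number of practices, and the 6 is an approximate input to the design effect. The gap is equally compatible with inviting everyone and losing some to refusal. Refusal is no safe harbour, though, because participants are unblinded too.

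A reader might also put an upper bound on the bias: if one arm enrolled every eligible patient at goal, it would start at 0.10 / 0.625 = 16%, against 10% in the other. That is not a bound on the difference, since the other arm could be selected downwards. It also presupposes complete selection in every practice of one arm and none in the other. It should not be used as the size of the problem.

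Finally, the Discussion says half the participants come from the earlier trial. For them the candidate list was fixed years before, which limits whom a GP can consider. It does not determine which of them are approached or agree.

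What remains is the written rule itself. It gives inclusion to an unblinded GP with a minimum and a loose criterion, and the analysis described has no adjustment that would absorb a resulting imbalance.

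**Conclusion.** The point holds as a vulnerability, not as a demonstrated bias. Followed as written, the plan allows patient inclusion to depend on the arm, through GP choice, patient refusal or both. The primary analysis as described corrects only for clustering.

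The illustrative size is a start of about 12% to 14% at goal in one arm instead of 10%. It rests on three assumptions: 10% at goal among all eligible patients, a 1.25- to 1.5-fold relative chance of inclusion for those at goal in one arm, and no selection in the other arm. The direction is not known.

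If the full protocol fixes the patient list before disclosure, the recruitment part of the concern is largely met and the article needs only to say so. The case for baseline adjustment and for reporting the recruitment numbers remains.

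**What to change.** **If inclusion is still open:** state that the research centre lists all eligible patients of both types in each practice before allocation is disclosed, and that all of them are invited, or that invitations follow a random order. Apply the judgement-based exclusions at that stage. The dates given for the second patient type (2012-2014) and publication in February 2015 suggest that inclusion may be largely complete, in which case the next two steps carry the weight.

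**In any case, adjust the primary model** for baseline goal status, or for baseline HbA1c, blood pressure and cholesterol. These are already collected in both groups. The baseline values have one advantage: in the intervention arm the treatment option and its targets are agreed at the first study visit, so goal status would need a definition that does not depend on that choice. Keep the covariates few, since the planned proportions imply only about 75 × 0.10 + 75 × 0.30 = 30 patients at goal at 24 months, before dropout.

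**In any case, report** the numbers eligible, invited and included, with baseline goal status, by arm. This separates GP choice from refusal and lets readers judge how comparable the arms were.

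**Cost:** one list per practice from existing records, a short addition to the analysis text, and an extended flow diagram. The limit is that adjustment for measured baseline values does not remove differences in unmeasured motivation, so it supplements the recruitment safeguard and does not replace it.
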